#### **8.3.4. Treatment compliance**

The investigator will monitor treatment compliance by counting the medication sachets/tablets returned by the patient at each visit.

#### **8.3.5. Collection of adverse events**

Possible adverse events will be recorded at all controls. See section 9 of the protocol.

## **9. ADVERSE EVENTS**

### **9.1. General Information**

An Adverse Event (AE) is any untoward medical event that befalls a clinical research patient or subject treated with a medicinal product, which does not necessarily have a causal relationship with the use of the treatment. An AE is therefore any unfavourable and unintentional sign (including an abnormal laboratory finding), symptom or disease temporarily associated with the use of a medicinal product (research or marketed), whether or not it is regarded as related to the product. An Adverse Event (AE) is any clinically significant disease, sign, symptom or abnormal laboratory finding which has appeared or deteriorated during the course of a clinical trial, regardless of its causal relationship with the investigational drug. The collection of information on non-serious AE should begin following the first administration of an investigational product. Serious AEs should begin to be collected once the subject's informed consent to participate in the study has been obtained.

AEs may be reported spontaneously or during the interview and physical examination of a subject. All AEs identified should be noted and described in the relevant page of Serious or Non-serious AEs in the CRF. If the diagnosis of the disease or underlying disorder is known, it will be included instead of the individual symptoms.

Subjects who have AEs that lead to the interruption or suspension of treatment with the investigational product, or those who have AEs that are maintained at the end of their participation in the study, should be monitored, as applicable. If possible, the result of any AE leading to permanent suspension or which is present at the end of the study will be reported, particularly if the AE was regarded by the investigator as definitely, probably or possibly related to the investigational product.

### **9.2 Non-serious Adverse Events (NSAEs)**

Any AE not classified as serious, as defined below, must be noted on the non-serious AE page of the CRF. These AEs will be followed up until they are solved or stabilise, and will be reported as SAEs if they become serious.

### **9.3 Serious Adverse Events (SAEs)**

A serious adverse event should be logged on the Serious Adverse Events (SAE) page of the CRF and should be communicated promptly to comply with the requirements of the regulatory authorities.

A Serious Adverse Event or Serious Adverse event is any untoward medical event which, at any dose:

- Causes death
- Is life-threatening (defined as an event in which the life of the patient or subject were endangered at the time of the event, and does not refer to an event that could have been fatal had it been more serious)

- Requires or prolongs hospitalisation
- Leads to a persistent or significant disability/incapacity
- Is cancer
- Is a congenital anomaly or birth defect
- Is an overdose (defined as accidental or intentional intake of any dose of a product that is regarded as excessive and medically important),
- Leads to dependence or drug abuse
- Is a major medical event (defined as a medical event which, while perhaps not immediately life-threatening, may be fatal or lead to hospitalisation, but which based on a suitable medical or scientific judgement may compromise the patient or subject or may require intervention [e.g. medical, surgical] to prevent a serious consequence, as defined above. Examples of major medical events will include, although this list is not to be regarded as exhaustive, intensive treatment of allergic bronchospasm, either in the emergency department or at home, as well as blood dyscrasia or convulsions that do not require hospitalisation.

To comply with the requirements of the regulatory authorities, adverse events classified as "serious" must be handled quickly and reported immediately to the Person in charge of Pharmacovigilance at Madaus.

Any serious AE which in the opinion of the investigator, is definitely, probably, possibly, probably not related or not related to the investigational product must be notified by telephone, wherever possible. Nevertheless, all serious AEs, whether or not they are related to the investigational product, should be reported immediately by fax, and the completed SAE report sheet subsequently sent by mail, as recorded in the CRF. Transmission by fax does not replace the obligation to send the SAE report sheet by mail. A courier service may be used instead of fax. A follow-up report will be required if only limited information is initially available.

#### **9.4. Notification of Adverse Events to the Health Authorities**

##### ***Prompt notification to the Spanish Medicines Agency***

The sponsor will notify the AEM of *all serious and unexpected events* that may be related to the investigational medicinal product (suspicion of serious and unexpected adverse event) whether they have occurred in Spain or in other countries, and whether they have occurred in the authorised clinical trial or in other clinical trials or in a different context of use. However, for medicinal products marketed in Spain used in the authorised conditions, only the suspicion of serious and unexpected adverse events that occur in the actual trial, either inside or outside Spain, if the trial is multinational, will be reported.

The maximum term of notification will be 15 calendar days as of the moment they become known. When the suspicion of serious and unexpected adverse event has caused the death of the subject, or threatened his life, the sponsor will notify the AEM within a maximum term of 7 natural days as of the moment the sponsor learns of the case. This information should be completed, as far as possible, within the following 8 days. For adverse events that occur in clinical trials performed in Spain, the number assigned by the AEM to the corresponding protocol should be mentioned, as well as the PEI (Spain's equivalent to Investigational New Drug, IND) number, as applicable. In the case of adverse events that occur outside Spain, reference will be made to the number assigned by the AEM to the PEI and/or clinical trials affected.

When this type of suspicion of adverse events occurs in a double-blind trial, the specific patient treatment code should be unmasked for the purpose of notification. Whenever possible, blinding shall be maintained for the investigator and for the person in charge of the analysis and interpretation of the results, as well as drawing up the study conclusions. In cases where this system of notification may be considered to interfere with the validity of the study (for example, when the primary endpoint is the occurrence of death) a specific system of notification may be agreed to with the AEM.

The suspicion of adverse events ascribable to the placebo will not be subject to this individualised system of notification.

Notifications should be addressed to the *Subdirección General del Medicamentos de Uso Humano* (Subdirectorate General of Medicinal Products for Human Use) by fax if the adverse event occurs in Spain: ([contact]) or else by post or delivered personally to the *Unidad de Registro y Tasas* (Registration and Fees Unit) of the AEM: ([name]) if they occur outside Spain. Only Spanish, the official language of the State, will be accepted for notifications of adverse events that occur in Spain. English will also be accepted for those occurring outside Spain. The notification form given in Annex I of this circular will be used for

notifications of suspicion of adverse events that occur in Spain. The CIOMS I form may be used for notifications of suspicion of adverse events that occur outside Spain.

In the case of *marketed medicinal products used according to the authorised conditions* (including the control medicinal product), these notifications will be sent to the Division of Pharmacoepidemiology and Pharmacovigilance of the AEM (not to the Subdirectorate General of Medicinal Products for Human Use). If the adverse events occur in Spain they should be faxed ([contact]). They will only be accepted if they are written in Spanish, the official language of the State. Any adverse events occurring outside Spain should only be sent by Post or delivered personally to the Registration and Fees Unit of the AEM ([name]). They will also be accepted in English. The notification form given in Annex I of this circular will be used for notifications of suspicion of adverse events that occur in Spain. The CIOMS I form may be used for notifications of suspicion of adverse events that occur outside Spain.

### **Prompt notification to the IEC and to the competent organs of the Autonomous Communities**

The sponsor will notify the IEC and competent organs of the Autonomous Communities where the trial is being conducted (see list in ANNEX A), individually and within the maximum term of 15 days, of all the suspected adverse events which are serious and unexpected and related to the investigational product occurring in patients recruited in their respective areas (or in other words, notify the IEC of reactions corresponding to the patients recruited in their health centre or area and notify the Autonomous Communities of reactions occurring in patients recruited in the Autonomous Community in question). This deadline will be 7 days for suspected adverse events that lead to death or are life-threatening.

The sponsor will report any other information on serious and unexpected adverse events associated with the investigational medicinal product (that occur in Spain or outside Spain) if so requested by the IEC when the protocol is reported, if so required by the specific regulations of the Autonomous Communities and in any case if the information represents a substantial change in the safety profile of the investigational product.

The reporting of safety information by the sponsor to the investigators will comply with the specifications in the ICH Good Clinical Practice guidelines.

### **Safety reports**

In addition to prompt notification, clinical trial sponsors will prepare a report evaluating the safety of the investigational medicinal product, taking all the available information into account. This report will be submitted to the AEM (Subdirectorate General of Medicinal Products for Human Use), to the competent organs of the corresponding Autonomous Communities and to the IEC that gave a favourable report to the trial, annually until the end of the trial and whenever requested by the Health Authorities or the IEC. It will include a list with all the suspected serious

adverse events reported inside and outside Spain, classified by organs and systems following the MedDRA classification, and an evaluation report will be made on the safety of the product for the trial subject (in the case of marketed products used in the authorised conditions, this list will only refer to suspected serious adverse events occurring in the clinical trial in question). It will also specify, as the case may be, the measures proposed to minimise the risks found. Finally, explicit justification will be provided of the possible need to modify or renew the informed consent, as well as the Investigator's Brochure. This report will not replace the application of amendments to the protocol, which will continue with its specific procedure.

Without prejudice to the frequency of safety reports indicated, the sponsor will prepare an *ad hoc* evaluation report whenever there is a relevant safety problem. This report will be submitted without delay to the AEM, the competent organs of the Autonomous Communities and the IEC concerned.

The safety report may be a part of the corresponding annual and final reports or be prepared separately. In any case, the annual and final reports will contain all the adverse events, in tabulated form, detected in the trial up until the time of the preparation of the report.

The safety reports, as well as the annual and final reports, should be written in Spanish, the official language of the state.

### **9.5. *Abnormal laboratory findings***

Besides being recorded on the relevant laboratory test results pages of the CRF or being sent electronically to a central laboratory, any result of a laboratory test that fulfils the serious adverse event criteria (see Section 9.3) should also be recorded on the SAE page of the CRF so that the Person in charge of Pharmacovigilance can collect additional information on the abnormal finding, including information on its relationship with the investigational product or other causes, action taken and resolution.

### **9.6. *Other Safety Considerations***

Any clinically significant change recorded during the intermediate or final physical examinations, electrocardiograms, radiographies or other potential safety evaluations, whether these procedures are required by the protocol or not, must also be recorded on the appropriate AE page (that is, NOT SERIOUS or SERIOUS) of the CRF so that the Person in charge of Pharmacovigilance can collect additional information on the abnormal finding, including information on its relationship with the investigational product or other causes, action taken and resolution.

### 9.7. *Imputability criteria*

The following imputability criteria are used in this study:

- **Certain** when there is a reasonable causal relationship between the investigational drug and the SAE. The episode improves with the withdrawal of the investigational drug and reappears when the drug is resumed, provided it is clinically viable.
- **Probable** when there is a reasonable causal relationship between the investigational drug and the SAE. The event improves with the withdrawal of the investigational drug. Treatment need not be restarted.
- **Possible** when there is a reasonable causal relationship between the investigational drug and the SAE. There is insufficient information on the withdrawal of the investigational drug or it is not very clear.
- **Improbable** when there is a temporary relationship with the administration of the investigational drug but there is no reasonable causal relationship between the investigational drug and the SAE.
- **Not related** when there is no temporary relationship with the administration of the investigational drug (too early, late or not taken) or there is a reasonable causal relationship between the SAE and another drug, intercurrent disease or circumstance.

The categories of *certain*, *probable* and *possible* are regarded as being related to the investigational drug. The categories of *improbable* and *not related* are regarded as not being related to the investigational drug.

The expression “reasonable causal relationship” means that there are facts (evidence) or arguments that suggest a causal relationship. If the information on the SAE is insufficient or contradictory, the event should be regarded as possibly related until further information is available. Since these events may be promptly reported, each investigator should do his utmost to collect all the extra information necessary.

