#### **C. Description of the investigational products**

##### **Investigational drug:**

Generic name: *Plantago ovata* husk  
Presentation: Sachets with 5 grams of granulate. Corresponds to 3.5 g of fibre.  
Sample manufacturer: Madaus S. A.  
Trade name: Plantaben

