##### **Placebo:**

Microcrystalline cellulose + excipient

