### 6.3. Sample size

#### Total sample: 290 patients (145 per group)

The results of an earlier study by Sprecher 1993, measuring the effect of 10.2 g of *Plantago ovata* a day in the reduction of the levels of LDL cholesterol were used to calculate the sample.

The value of the effect to be detected ( $d = 7.5$  mg/dl) is equivalent to a reduction of 5% of LDL in patients with LDL baseline values of 150 mg/dl.

The working hypothesis is:

$$H_0: \Delta \text{LDL } \textit{plantago ovata} - \Delta \text{LDL placebo} < |7.5| \text{ mg/dl}$$

$$H_1: \Delta \text{LDL } \textit{plantago ovata} - \Delta \text{LDL placebo} \geq |7.5| \text{ mg/dl}$$

Where  $\Delta \text{LDL} = \text{final LDL} - \text{baseline LDL}$

For a statistical significance of  $\alpha = 0.05$  and a power of 80%, with a standard deviation of 20 mg/dl in the  $\Delta \text{LDL}$ , the sample size required to detect significant differences of 7.5 mg/dl between the group treated with *Plantago ovata* and the group treated with placebo is 112 patients per group, for which, adjusted to an expected percentage of losses of 15%, a total of **270 patients** will be required.

After treatment, approximately 75% of the patients treated with soluble fibre (84 patients) and 85% of those treated with placebo (95) will not have 130 mg/dl of LDL-C in plasma. A statin will be added to all these patients' treatment.

It is assumed that the combination of soluble fibre with statins will cause the mean value of LDL-C to fall from 157 mg/dl to 125.6 mg/dl ( $\Delta \text{LDL}$  soluble fibre + statin = 31.4 mg/dl). In the placebo + statin group from 161 mg/dl to 136.85 mg/dl ( $\Delta \text{LDL}$  placebo+statin = 24.15 mg/dl).

For a statistical significance of ( $\alpha=0.05$ ), a power of 80%, a standard deviation in the  $\Delta \text{LDL}$  of 18.5 mg/dL and a ratio of 0.85 between groups treated with placebo for 0.75 treated with soluble fibre, **the sample size** necessary to detect differences of

7.25 mg/dl in the  $\Delta$ LDL between the group treated with statin+soluble fibre and the group treated with statin + placebo is 111 patients in the placebo group and 98 patients in the soluble fibre group.

As the percentage of failure in the objective of LDL-C equal to or lower than 130 mg/dl is 75% in the patients treated with soluble fibre and 85% in those treated with placebo, adding a 10% of patients lost to follow-up means that a **total sample of 290 patients (145 per group)** will be required.

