### **Visit S8 (Day 56± 3)**

The participants will go to the hospital for a visit addressing the following aspects:

➤ *Clinical*

A clinical history similar to that of S0 will be made

Identify the presence of clinical problems, concomitant treatments, etc.

Collection of adverse events.

Blood pressure and weight will be taken.

➤ *Analytical*

The results of the mean LDL-C value obtained in the two analyses made in the previous week (S7), at most 3 days before visit S8, will be noted. Similarly, the values obtained in the analyses on the last day of S7 will be noted as final parameters of the biochemistry and haematological trial.

➤ *Dietary*

The patients will already have returned the 3-day record the day they went to the hospital for the second blood sample extraction.

The dietician will address the diet follow-up and possible deviations. If the patient has to continue in the study he/she will be given diet guidelines according to his energy needs.

➤ *Medication*

Evaluate compliance with treatment with fibre. The patient should return used and unused medication containers.

**Two situations may arise at this point: 1) The patient has reached the therapeutic objective (LDL-C < 130) and will end the study, or 2) the patient will present an LDL-C ≥ 130 mg/dl and will continue with the same treatment with a statin (Simvastatin) added for a further 8 weeks.**

**The instructions on how to administer the fibre, the Simvastatin and, as the case may be, the patient's regular medication will be gone over once again.**

If the patient is to continue in the trial, the investigator will issue the same medication that the patient was taking + a statin in sufficient quantity for 4 weeks until visit S12.

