## **12.4. Analysis populations**

The statistical analysis will be performed both for intention to treat (each patient is analysed in the group he/she was assigned to at the beginning of the study regardless of whether he/she did not comply with the corresponding intervention) and by protocol, which only includes patients who complied suitably with the intervention that was assigned to them.

The safety analysis will include all the patients who received study medication; the adverse events in each treatment will be described graphically and/or numerically.

The Spanish version 11 of the statistical application package SPSS will be used for the data analysis.

A two-tailed significance of 0.05 will be considered in all statistical tests.

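### The serious-event causality scale has no place for simvastatin, a drug the protocol itself gives from week 8, so a reaction attributed to it is coded as not related

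*Protocol*

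**What the plan says.** Section 3.C of the protocol, under "Investigational drug", gives "Generic name: *Plantago ovata* husk". The placebo is listed beside it as "Microcrystalline cellulose + excipient". Simvastatin does not appear in the visible part of that section.

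Section 9.7 sets five causality grades. Each refers to the investigational drug in the singular. The lowest, *Not related*, applies among other cases when "there is a reasonable causal relationship between the SAE and another drug, intercurrent disease or circumstance". *Certain*, *Probable* and *Possible* count as related; *Improbable* and *Not related* do not.

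Under section 8.2, Visit S8, a patient with LDL-C at or above 130 mg/dl "will continue with the same treatment with a statin (Simvastatin) added for a further 8 weeks". Section 7.1 says the same. Section 4.2 lists the combined effect of husk and statin among the secondary objectives.

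Section 9.4 requires expedited notice to the medicines agency of serious and unexpected events that may be related to the investigational product. Notice to the ethics committees and regional authorities also depends on a relation to that product. In a double-blind case the treatment code is opened for the notice. The section adds: "The suspicion of adverse events ascribable to the placebo will not be subject to this individualised system of notification".

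**The concern.** A causality scale should let the investigator say which of the treatments given by the trial is suspected. Here the clause on other drugs is not limited to drugs from outside the protocol. Simvastatin, supplied by the trial and part of a studied combination, therefore falls on the same side as an unrelated concomitant medicine or an intercurrent illness.

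Two things are at stake. The first is the safety record of the second period: an SAE the investigator puts down to simvastatin is filed as unrelated, and an SAE that could be due to either drug or to both has no settled grade. The second is onward reporting, since the expedited triggers depend on a relation to the investigational product.

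**Working it through.** The point rests on wording, so the sections are followed in order. Arithmetic is needed only for the number of patients exposed.

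**Number exposed to simvastatin**

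- Inputs from section 6.3: 112 evaluable patients per group, and "approximately 75% of the patients treated with soluble fibre (84 patients) and 85% of those treated with placebo (95") expected to miss the goal and have a statin added.
- Reproducing the protocol's counts: 0.75 × 112 = 84.0 and 0.85 × 112 = 95.2, which match the stated 84 and 95.
- Total: 84 + 95 = 179 of 2 × 112 = 224, or 80%.
- The same shares applied to the 145 randomised per group, assuming no losses: 0.75 × 145 = 108.75 and 0.85 × 145 = 123.25, together 232 of 290, again 80%.

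**Case 1: SAE attributed to simvastatin alone**

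1. The reference product in 9.7 is the investigational drug, which in the visible text of 3.C is the husk.
2. Simvastatin is then another drug, so the *Not related* clause applies.
3. *Not related* counts as unrelated to the investigational drug.
4. The triggers in 9.4, for the agency and for the committees and regions, require a suspected relation to the investigational product. The event does not meet them. This holds equally in both arms.

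**Case 2: SAE plausibly due to both drugs**

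1. A reasonable causal link to the husk, without clear information on withdrawal, satisfies *Possible*.
2. A reasonable causal link to simvastatin satisfies *Not related*.
3. Section 9.7 gives no rule of precedence, so one event meets a related and an unrelated grade together.

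**Case 3: unclear SAE**

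Section 9.7 treats an event with insufficient or contradictory information as possibly related until more is known. This covers the event only while it stays unclear. Once simvastatin is accepted as the cause, Case 1 applies.

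**The case against.** Several safeguards stand and limit the point.

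- Section 9.3 sends every SAE to the sponsor at once, whatever its relation to treatment. Sections 9.5 and 9.6 have pharmacovigilance collect information on other causes. The safety-report part of 9.4 puts all adverse events in tables in the annual and final reports and calls for an ad hoc report on any relevant safety problem. Nothing goes uncollected.
- Section 9.4 has separate wording for medicinal products marketed in Spain and used as authorised, and for the control product. It can fairly be read to cover simvastatin. But it does not name simvastatin and adds no causality grade for it, so how it fits with the investigational-product trigger is left open.
- Only unexpected serious reactions are expedited in any case.
- The text that follows the placebo entry in section 3 is not in the copy at hand. If simvastatin is listed there, the literal reading weakens. The case report form and the sponsor's procedure for assessing SAEs are also not shown, so a missing field on the form cannot be assumed.

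Three stronger readings are tempting, and the document does not support them.

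- A reader might infer that simvastatin reactions in the placebo arm are lost through the placebo exemption. The exemption works by cause, not by arm: an event suspected to be due to simvastatin is not ascribable to placebo. The most that can be said is that the wording does not make this explicit for an event left at *Possible* under blinding and then unmasked.
- A reader might infer that a joint reaction can never be recorded as related. It can, under *Possible*; the fault is that *Not related* fits as well.
- A reader might infer from section 12.4, where "the adverse events in each treatment will be described graphically and/or numerically", that the tables pool the periods before and after S8. The text does not say so, and table layout belongs to the analysis plan.

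**Conclusion.** The point holds as a gap in causality coding, and possibly in onward expedited notice, but not in the collection of SAEs. Followed literally, section 9.7 codes an SAE attributed to simvastatin as unrelated and leaves one plausibly due to both drugs with two contradictory grades. On the protocol's own shares this concerns the SAE assessments of about 80% of patients from S8 (179 of 224 evaluable).

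That figure counts exposure, not affected events. The documents give no rate of serious simvastatin reactions, so the number of miscoded or unreported events cannot be estimated; for expedited notice, only serious and unexpected reactions matter. The conclusion assumes that the visible text of 3.C is complete as to what counts as the investigational drug, and that no unseen form or procedure already asks for a separate grade. It is a worthwhile and inexpensive improvement to the safety record, not a threat to the efficacy result.

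**What to change.** In section 9.7, from S8, have the investigator grade each SAE separately against the blinded product and against simvastatin, with an option for both. Limit the other-drug clause under *Not related* to drugs not given by the protocol.

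In section 9.4, reconcile the investigational-product trigger with the wording on marketed and control products. State explicitly that a suspected serious and unexpected reaction to simvastatin is covered in either arm and is not treated as ascribable to the placebo.

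The cost is one extra field on the SAE form, a few lines of protocol text and possibly a few more expedited reports. No visit or treatment changes.
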